### Sample Size for a Future RCT

Based on pilot effect sizes and variability estimates, a future definitive RCT would require approximately 175 participants per arm (350 participants in total) to detect moderate effects (*d*=0.5), considering 80% power, *α* of .05, and 15% attrition. Pilot findings will refine these projections.

### Assignment of Interventions (Allocation)

Sequence generation is performed through computer-generated randomization using Python (numpy.random.RandomState with seed=42 for reproducibility). Participants are stratified by sex (male/female) to ensure balance. Block randomization with randomly permuted block sizes (2, 4, 6) is used to maintain unpredictability while ensuring approximately equal group sizes throughout recruitment. The approach is implemented using numpy, hashlib, and pandas libraries.

### Allocation Concealment Mechanism

The randomization sequence is stored in a password-protected file accessible only to the researcher. Allocation is revealed only after the participant completes the baseline PSQI and receives the device (day 0), preventing selection bias. Participants are enrolled and allocated in cohorts of 2‐8 to maintain seasonal balance across the 15-month recruitment window.

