### Implementation

The researcher generates an allocation sequence and assigns interventions according to the sequence concealed in sealed, sequentially numbered envelopes, which are opened only at the allocation time point. Participants are informed of group assignment on day 30 (intervention delivery) for the experimental group or at close-out for the control group.

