### Seasonal Control

To account for seasonal or environmental factors over the 15-month recruitment window, device assignment ensures equal representation from both groups at each time point. An even number of participants receive devices simultaneously, preventing differential seasonal effects between groups.

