### Blinding (Masking) Level

This is an open-label pilot trial with partial blinding where feasible. Participants become aware of group assignment at different time points (experimental group participants are informed on day 30 at intervention delivery; control group participants are informed on day 60 at close-out). Samsung Galaxy Watch 4 automatically records objective sleep data independent of participant or researcher knowledge, eliminating measurement bias for the primary outcome. The researcher analyzing primary outcome data (Samsung scores) remains blinded to group allocation, and unblinding occurs on day 30 to identify participants for analysis in the experimental group in order to provide personalized recommendations.

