### Data Management

Data entered and collected by Samsung Galaxy Watch 4 are automatically synced to Samsung Cloud (encrypted transmission) upon pairing. The PSQI forms are completed on paper, and the information is manually entered by the researcher into a password-protected spreadsheet with self-verification (data entered twice by the researcher to ensure accuracy). All data stored on the researcher’s local computer are encrypted, providing additional privacy protection through local-only storage. Moreover, data are stored in 2 separate local files as a backup measure for protection against file corruption. Access control is set, with only the researcher having access to all study data, including identifiable information linking Participant_ID to personal information. No other personnel have access to the data.

Data security involves (1) physical security (paper PSQI forms are stored in a locked filing cabinet at a secure location), (2) digital security (electronic files are password-protected and encrypted, and are stored on the researcher’s local computer only [no remote or cloud storage of identifiable data]), and (3) transmission security (Samsung device data download uses encrypted protocols [HTTPS]).

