### Interim Analysis

No formal interim analysis is planned. The researcher conducts data quality monitoring but does not analyze outcomes until study completion to prevent bias.

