### Accountability Framework

The accountability framework involves the following aspects:

Adverse events from artificial intelligence (AI): If ML-derived recommendations cause participant harm (eg, a recommendation to reduce sleep duration leads to excessive daytime sleepiness affecting work safety), the event is documented as an adverse event. The researcher notifies the ethics committee, and an investigation is conducted to determine if a systematic model error exists.Replication and audit: The ML code, trained models, and analysis scripts are made available to the ethics committee and peer reviewers upon request.Model performance monitoring: During the study, the principal researcher monitors whether the experimental group shows unexpected negative outcomes (eg, worsening sleep scores), triggering a review of ML recommendation patterns for systematic errors.

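### One researcher makes, holds and uses the allocation list and alone sees the data, so the claimed concealment, blinded analysis and equal cohorts are not delivered

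*Protocol article*

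**What the plan says.** **Allocation.** Assignment of Interventions describes blocks of 2, 4 and 6 within sex, generated with "numpy.random.RandomState with seed=42 for reproducibility", and promises only roughly equal arms. Allocation Concealment Mechanism adds: "The randomization sequence is stored in a password-protected file accessible only to the researcher". It has allocation revealed on day 0, after the baseline PSQI and device handover, and states that this prevents selection bias. Implementation says: "The researcher generates an allocation sequence and assigns interventions according to the sequence concealed in sealed, sequentially numbered envelopes".

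**Cohorts.** Participants enter in cohorts of 2 to 8. Seasonal Control says "device assignment ensures equal representation from both groups at each time point", on the ground that an even number of people receive devices together.

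**Blinding and access.** Blinding (Masking) Level says "The researcher analyzing primary outcome data (Samsung scores) remains blinded to group allocation" and, later in that sentence, places unblinding on day 30. It also says automatic recording removes measurement bias for the primary outcome. Data Management limits access to the researcher: "No other personnel have access to the data".

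**Looking at outcomes.** Under Interim Analysis the researcher "does not analyze outcomes until study completion to prevent bias". Under Accountability Framework, "the principal researcher monitors whether the experimental group shows unexpected negative outcomes (eg, worsening sleep scores").

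**The concern.** Concealment protects a trial only if the person deciding who enters, and when, cannot know the next assignment. Here the list is open to the person who takes consent. Blinded analysis protects it only if the person deciding which nights and participants count does not know the arm. Here no second person has the data. A published report that repeated the protocol's wording would claim safeguards the trial did not have.

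For the primary outcome the matter is narrower than it first looks. The watch produces the score, so knowing the arm cannot alter a recorded night. It can affect which nights and participants are kept, wherever the rules leave room for judgement. The equal-cohort claim matters less, but it is presented as the control for seasonal effects and it does not follow from the stated scheme.

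**Working it through.** **1. Who does what.**

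| Task | Person named | Section |
|---|---|---|
| Generates the sequence, assigns from it | the researcher | Implementation |
| Sole access to the list | the researcher | Allocation Concealment Mechanism |
| Trained to obtain consent | the principal researcher | Informed Consent Collection |
| Explains the personalised advice | the researcher | Intervention Delivery and Verification |
| Reviews all model output | the principal researcher | Human Oversight |
| Sole access to study data | the researcher | Data Management |

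A password and envelopes cannot hide a list from the person who wrote it and keeps it.

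**2. When allocation becomes known.** Allocation Concealment Mechanism gives day 0; Blinding (Masking) Level gives day 30. Participants are told on day 30 (experimental) or at close-out (control), so the natural reading is that the day-0 reveal is to the researcher. On either date the arm is known before the outcome period, days 31 to 60, begins. The sole data holder therefore cannot be a blinded analyst.

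**3. Where judgement enters.** The article says it contains the complete analysis plan and that no separate one exists, so these points are not settled elsewhere:
- More than 20% of nights missing: exclusion is optional in Adherence Assessment and mandatory in Data Collection Quality Control.
- Outliers: they lead to replacement in Data Collection Quality Control, but are only flagged (beyond 3 SD) in Data Preprocessing Pipeline.
- Artifact conflicts: nights are excluded, with no criterion given at that place.
- Participants without sufficient nights are excluded (Exploratory Analyses, missing-data text); sufficiency is not defined there.

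**4. Equal cohorts.** The plan's own figure is a guarantee, that is, probability 1. A hand check for cohorts of 2, assuming the three block sizes are equally likely:
- Two people of the same sex on consecutive paired places in a block of size b get one arm each with probability (b/2)/(b−1): 1 for b = 2, 2/3 for b = 4, 3/5 for b = 6.
- Such blocks hold 1, 2 and 3 pairs, so the average is (1×1 + 2×2/3 + 3×3/5)/(1+2+3) = 4.133/6 = 0.689.
- One man and one woman come from independent sequences, so the probability is 0.5.

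Simulation of the stated scheme (32 participants, 3,000 trials per setting) extends this to larger cohorts. Sex order is not given, so it was varied as an assumption. Entries are the probability that a cohort of the given size splits equally. The last column is the range, over cohort sizes, of the probability that every cohort in the trial does.

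| Sex order | 2 | 4 | 6 | 8 | Mixed | All cohorts equal |
|---|---|---|---|---|---|---|
| Random 50:50 | 0.570 | 0.484 | 0.484 | 0.465 | 0.501 | 0.0007 to 0.115 |
| Alternating | 0.505 | 0.528 | 0.433 | 0.522 | 0.470 | 0.0007 to 0.185 |
| Same-sex pairs | 0.696 | 0.537 | 0.560 | 0.527 | 0.582 | 0.029 to 0.180 |
| One stratum only | 0.692 | 0.678 | 0.722 | 0.708 | 0.692 | 0.039 to 0.428 |

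The entries for cohorts of 2 agree with the hand values (0.696 and 0.692 against 0.689; 0.505 against 0.5). With two strata, a cohort of 2 falls wholly in one arm 30% to 50% of the time. Enforcing an equal split would mean departing from the list.

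**5. Can allocation be re-timed?** Recruitment ended in July 2025 and the last possible end date is 31 December 2025. A 60-day participant must therefore start by about 1 November, and the article cites a funding reference dated 24 November 2025. With allocation at day 0, everyone is already allocated.

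**The case against.** The strongest reply is that this is a disclosed open-label pilot, meant for feasibility and hypothesis generation, with a device-generated primary outcome. That stands, and it lowers the severity. It does not rescue specific claims that go beyond the disclosure.

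Nor does any single sentence say that one person does everything. Screening is described in the passive, Study Setting speaks of a researcher, and the access section for enrolled participants mentions authorised personnel. The tasks tabulated above still support the reading, and that access section also limits full access to the principal researcher.

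A reader might infer more than the documents support:
- *That about 18% of nights are excluded with the arm known.* That figure covers all 60 days and all quality criteria. Most of those in Data Preprocessing Pipeline are mechanical, such as missing segments, clock limits and a 30-minute discrepancy.
- *That the fixed seed is itself a fault.* It makes the list reproducible, but the researcher can read the list anyway.
- *That the harm monitoring is a hidden interim analysis.* It is a trigger for reviewing recommendation patterns, which only one arm receives. The text does not say that only this arm is watched, and a per-participant low-score rule applies without regard to arm. What is missing is a statement that makes it agree with Interim Analysis.
- *That entry or exclusions were in fact manipulated.* Nothing in the protocol shows this. The point is that the stated safeguards would not prevent it.

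**Conclusion.** The concern holds in this form: three stated protections are not provided by the procedures described. Concealment does not reach the enrolling researcher, no blinded analyst exists, and equal cohorts are not ensured. The first two rest on reading the researcher and the principal researcher as one person, which the sections taken together support.

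Only the third has a size. An even cohort splits equally about 43% to 70% of the time with two sex strata, and about 68% to 72% with one. All cohorts are equal in under 1% to about 18% of two-strata trials. These figures depend on the assumed sex order, cohort sizes and equally likely block sizes, but no setting comes near a guarantee. The bias from selective entry or exclusion cannot be quantified from the document, and the share of nights open to judgement is unknown.

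This should be fixed before analysis. It is not a reason to redesign a pilot whose recruitment is over.

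**What to change.** Before analysis:

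1. Resolve Adherence Assessment, Data Collection Quality Control, Data Preprocessing Pipeline and the missing-data text into one set of night and participant exclusion rules. Freeze it as a script, run it on all nights without the group column, and only then merge allocation. Report exclusions and replacements by arm. The section on excluded participants has their data deleted at once, so the script cannot reach nights already destroyed; for those, keep and report the counts and reasons by arm.
2. Withdraw or restate the claims of prevented selection bias, a blinded analyst and ensured equal representation. Limit the measurement-bias claim to the recording of the score. Report lack of concealment from the enrolling researcher as a limitation, and tabulate the actual cohort-by-arm split.
3. Reconcile day 0 and day 30 as the time of allocation and unblinding. State that the harm monitoring makes no between-group comparison before data lock, so that it agrees with Interim Analysis.

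The cost is a short script and less favourable wording; no staff or visits are added.

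Moving allocation to the end of the baseline period, and giving the list to someone independent, are options for the future trial only. If equal cohorts are wanted there, blocks of 2 within same-sex pairs gave an equal split in every cohort in all 2,000 simulated trials. They also make the second member of each pair predictable, so an independent list holder would be essential.

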### Interventions

#### Control Intervention: Generic Sleep Hygiene Education

Control group participants receive standardized sleep hygiene education on day 30, covering general recommendations applicable to all adults. Examples include maintaining a consistent sleep-wake schedule and sleeping between 7 and 9 hours per night. These recommendations are not personalized to individual sleep patterns.

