### Participant Timeline

The measurement time points after eligibility screening, informed consent approval, and randomization in the control and experimental groups are presented in Figures1  2, respectively.

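### The protocol gives both day 0 and day 30 as the time the researcher learns the allocation; on the day-0 wording, baseline night exclusions and participant replacements can be made with the arm known

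*Protocol article*

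**What the plan says.** All references are to the protocol article.

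- **Allocation Concealment Mechanism:** "Allocation is revealed only after the participant completes the baseline PSQI and receives the device (day 0), preventing selection bias". The same section says: "The randomization sequence is stored in a password-protected file accessible only to the researcher".
- **Implementation:** "The researcher generates an allocation sequence and assigns interventions according to the sequence concealed in sealed, sequentially numbered envelopes". Envelopes are opened at the allocation time point, which is given no day. For participants: "Participants are informed of group assignment on day 30 (intervention delivery) for the experimental group or at close-out for the control group".
- **Blinding (Masking) Level:** "The researcher analyzing primary outcome data (Samsung scores) remains blinded to group allocation". The sentence then continues: "unblinding occurs on day 30 to identify participants for analysis in the experimental group in order to provide personalized recommendations".
- **Participant Timeline:** the measurement schedule is introduced as "The measurement time points after eligibility screening, informed consent approval, and randomization in the control and experimental groups", so randomization comes before all measurements.
- **Interventions:** "Control group participants receive standardized sleep hygiene education on day 30". The personalized advice is delivered on the same day.
- **Statistical Methods:** the only covariate is the mean sleep score over days 1-30.
- **Data Management:** only the researcher has access to the study data.

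**The concern.** Nothing distinguishes the arms until day 30, and the article gives no reason for revealing the allocation a month earlier. If it is revealed on day 0, the person who decides which baseline nights count, and which participants are dropped and replaced, can know each participant's arm while deciding.

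Two things are at stake. First, night exclusions that depend on the arm would shift the covariate in one arm and so shift the adjusted group difference. Second, participants lost in the first 30 days would be post-allocation losses, replaced by someone who may know the arm. If the envelope were opened on day 30, the same losses would come before allocation and could not affect the randomized comparison.

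**Working it through.** The plan gives no figure on this point to reproduce. The check is a comparison of sections, followed by two illustrations of scale.

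**1. When does the researcher learn the arm?**

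| Section | Event | Day |
|---|---|---|
| Allocation Concealment Mechanism | allocation revealed | 0 |
| Implementation | envelopes opened | not defined |
| Implementation | participants told | 30 (experimental) or close-out (control) |
| Blinding (Masking) Level | unblinding to select experimental participants | 30 |
| Interventions | first difference between arms | 30 |

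The participants' position is clear: none is told before day 30. The researcher's position is not. A single researcher generates the sequence, alone can open its file and alone has the data, so the day-0 reveal and the day-30 unblinding describe the same person and cannot both hold. Seasonal Control, which has device assignment secure equal representation of both groups, suggests that allocation is already in use at hand-over. On the day-0 wording, 30 of 60 nights (50%) lie between the reveal and the first difference between arms.

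**2. Is there room for discretion in that interval?** Many rules in the Data Preprocessing Pipeline are mechanical, such as the clock window and the 30-minute stage discrepancy. Others leave room:

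- Participants missing more than 20% of nights are excluded as an option under Adherence Assessment, but as a firm rule under Data Collection Quality Control.
- Outliers lead to replacement under Data Collection Quality Control, but are only flagged in the preprocessing pipeline.
- The missing-data paragraph requires enough nights in each period and gives no threshold.
- The access-control section for excluded participants has their data deleted at once, so these decisions cannot be re-examined later.

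**3. How would an arm-dependent covariate act?** In the planned model,

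adjusted difference = (difference in post means) − β₂ × (difference in baseline means).

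A shift of δ points in one arm's cleaned baseline mean therefore moves the adjusted difference by β₂ × δ. If β₂ were 0.6 to 0.8 (assumed; the document gives no value), that is 0.6 to 0.8 points per point of δ. Nothing in the document indicates that δ differs from zero.

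**4. How many exclusion decisions could there be?** Take the protocol's expected 18% night exclusion. Assume that excluded nights count as missing, that nights are independent, and that the rate is the same for everyone. The section does not say whether the 20% applies to 30 or 60 nights, so both are shown:

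- Over 30 nights, more than 20% means at least 7: P(X ≥ 7), X ~ Bin(30, 0.18) = 0.288, and 32 × 0.288 = 9.2 participants.
- Over 60 nights, more than 20% means at least 13: P(X ≥ 13), X ~ Bin(60, 0.18) = 0.276, and 32 × 0.276 = 8.8 participants.

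About 9 of 32 could meet the rule under these assumptions. Clustering of bad nights within participants would change the number. This counts occasions for a decision; it does not estimate bias.

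**The case against.** The strongest reply is that the protocol largely protects the baseline. Participants, who wear the watch and complete the PSQI on paper, do not know their arm. The watch records the score whatever the researcher knows. A covariate measured after randomization but before any intervention is unaffected by treatment and does not in itself bias an ANCOVA. All of this stands.

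A reader might infer several stronger points that the document does not support:

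- **That control nights are cleaned later or differently from experimental nights.** One preprocessing pipeline is given for everyone, with exclusions and reasons documented. The Blinding section says only that experimental participants are identified on day 30; a difference in cleaning times would be inference.
- **That the day-30 PSQI is compromised as an outcome.** It enters no planned between-group test; the secondary analysis uses the change from day 0 to day 60.
- **That the Participant Timeline adds a third conflicting date.** Randomizing, opening an envelope and unblinding for delivery can be separate events, and its wording fits either reading.

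It can also be said that a later opening does not blind someone who holds the list. That is correct: the change protects only if the sequence file is left unopened. Nor does it address losses in days 31-60. Finally, recruitment ended in July 2025, so re-timing may reach few or none of the current participants.

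**Conclusion.** The contradiction between the day-0 reveal and the day-30 unblinding is established by the text, and the undefined opening time leaves it unresolved. On the day-0 wording, the researcher's knowledge of the arm spans the whole covariate period for no stated purpose, and all days 1-30 losses fall after allocation. On the day-30 wording, baseline nights are collected blind, and the remaining question is whether they are cleaned before or after the envelope is opened.

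The exposure is limited to discretionary exclusion of nights and exclusion and replacement of participants. Its size cannot be derived: the β₂ range and the independence of nights are assumptions, and no arm-dependent shift is documented. The protocol should be corrected here, but this is not evidence that the primary analysis is biased.

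**What to change.** Bring Participant Timeline, Allocation Concealment Mechanism, Implementation and Blinding (Masking) Level to one stated time point: envelopes are opened on day 30, after the day-30 PSQI is completed and after the preprocessing rules have been applied to, and locked for, the baseline nights of every participant in the cohort. State that the sequence file stays unopened until then.

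For participants already allocated:

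- apply the preprocessing and exclusion rules identically in both arms, with the arm label masked;
- state which reveal time was actually used;
- report exclusions and replacements in days 1-30 by arm. Counts suffice, so this does not require data that have been deleted.

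The cost is modest: the existing scripts are run for controls as well, and each cohort's data must be downloaded and prepared before its envelopes are opened. Sex strata and blocks are kept. Because cohorts start together, they reach day 30 together, although an early dropout could leave a cohort uneven. No extra visits, staff or participants are needed. The planned larger trial should adopt the same order.
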